#### Training and inter-rater reliability

All outcome assessors will receive the necessary training in survey planning and relevant instruments, along with ongoing support and supervision. After completing the training, outcome assessors will be grouped, and each group will be assigned a leader (supervisor) who is a member of the study team.

The supervisor and trial manager will verify the accuracy and consistency of the data collected. During fieldwork, supervisor will monitor the interview process to ensure compliance with protocol specifications. Additionally, approximately 20% of all interviews will be randomly checked by supervisors for quality assurance.

#### Assessments

The CIC-PDD assessment approach and instruments incorporate both effectiveness and implementation outcome evaluations. The timing and content of the outcome assessments are delineated in Tables 1 and 2. The RE-AIM evaluation framework guides and informs the outcome assessments (Table 2). The primary effectiveness evaluations consist of patient-reported outcome measures, including assessments of the study’s primary and secondary outcomes (Table 1). Further detail regarding selected outcome assessments is described below.

**Table 2 Tab2:**
[figure not shown]
Key variables and data sources for assessment objectives

*IC*, Integrated Care; *EUC*, Enhanced Usual Care; *SCL-20*, The Symptom Checklist-20; *SF-12*, The12-Item Short Form Health Survey; *SDSCA*, Summary of Diabetes Self-Care Activities Questionnaire; *MTBQ*, Multimorbidity Treatment Burden Questionnaire; *MMAS*, Morisky Medication Adherence Scale; *PACIC*, Patient Assessment of Chronic Illness Care; *ORIC*, Organizational Readiness for Implementing Change; *LIM*, Level of Integration Measure; *PCCA*, Patient-Centered Care Assessment Tool

##### Primary outcome

The primary outcome in this trial is the change in depression symptoms scores (The Symptom Checklist-20, SCL-20) and glycemic control (HbA1c) from baseline to 6 and 12 months.

The use of the SCL-20 for outcome measurements is intended to minimize potential test–retest bias given the repeated use of the PHQ-9 for clinical care.

##### Secondary outcomes

To explore the causal mechanisms of CIC-PDD intervention, a number of secondary outcomes will be measured, using various instruments.Mental and physical health outcomesProportion of participants achieving significant reductions in individual outcomes: reduced depressive symptoms [≥ 50% reduction in SCL-20], glycemic control [HbA1c ≥ 0.5% reduction].Change in quality of life: general quality of life (The12-Item Short Form Health Survey, SF-12) [50] and disease-specific quality of life (Diabetes Quality of Life) [51].Change in behaviors and perceptionsSelf-management: Summary of Diabetes Self-Care Activities Questionnaire (SDSCA) [52]Burden of illness: Multimorbidity Treatment Burden Questionnaire (MTBQ) [53]Burden of treatment: Morisky Medication Adherence Scale (MMAS) [54]Experience of patient-centered and coordinated careProcess measures: Patient Assessment of Chronic Illness Care (PACIC) [55] Satisfaction with care: overall satisfaction. Implementation outcomes

We have observed a lack of results on organizational factors at a system level and healthcare providers’ factors in previous studies, which are essential for reducing fragmented care and improving continuity and coordination [28]. Therefore, we will measure context characteristics, changes in health providers’ attitudes, and CIC-PDD adherence, which will help us gain a better understanding of our results.Community characteristics: Organizational Readiness for Implementing Change (ORIC) [56]Care team attitudes and perceptions: Baseline clinician attitudes survey, Level of Integration Measure (LIM) [57], Project Satisfaction [58], Perceptions of Working in a Primary Health Care Team [59]Collaborative care adherence: Patient-Centered Care Assessment Tool (PCCA) [60], CIC-PDD Adherence Questionnaire

##### Health care utilization

Using a service utilization questionnaire and electronic health records, we collect the number of clinic visits and hospital admissions, the use of resource use and related costs measures.

These outcomes, instruments, and data sources are summarized in Table 2.

There will be no biological specimens collected.

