The CIC-PDD intervention encompasses the following components:Patient-centered assessment and engagement: patients are usually first assessed in their own residential setting or CM’s workplace. The severity of depression, diabetes-related conditions and the relationship between depression and diabetes will be evaluated. It also encompasses an assessment of associated behavioral and social deficiencies. The evaluation results are described and recorded in “Follow-up Booklet.”Measurement and monitoring-based care: depression symptoms and HbA1c are measured at all sessions. These data serve as references for adjusting the care plan and helping care team make reasonable decisions.Behavioral activation (BA)-based care: The care plan focuses on behavioral activation (BA), which highlights the importance of engaging in pleasant or meaningful activities. This approach aims to help patients reschedule activities to reintroduce positive reinforcement, improve thoughts functioning and raise mood, and reduce the frequency of avoidant behaviors and unhealthy lifestyle. In collaboration with CM, patients will draw up goal-oriented behaviors likely to improve mental and physical health, and self-monitor and implement related activities according to schedules (“Health Diary”). Notably, BA is an effective and acceptable technique similar to cognitive behavioral therapy (CBT) [43]. In addition, BA is chosen because it employs a more perceptive therapeutic approach than CBT, which is easily delivered by PCPs after a short period of professional training [44].Technology-based care—an official WeChat official account called “Integrated Care -CIC-PDD” will be developed to address the accessibility of the care plan.(3) Scheduled patient follow-ups

All patients will receive proactive follow-up and case management from the assigned CM. Each patient will have a maximum of 18 sessions (two phases) over 1 year. The sessions can be conducted in-person or telephone contacts, depending on patients’ preference and condition.The first phase (high-intensity): 1–12 session

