### Supervision and fidelity

CMs will receive ongoing supervision from health communicator and study staff. CMs need to keep and maintain notes for the patients using the “Follow-up Manual” during every session. This “Follow-up Booklet” reports how many sessions patients received, the delivery mode (in person or by telephone) in which they received intervention, PHQ-9 scores, blood glucose level, and what interventions patients accepted.

For each session, CMs are required to make audio recordings and take photos to document the process and capture important information. At the end of session, the CMs need to send the recorded materials to health communicator, who will review and evaluate them. A random selection of these materials will then be submitted to the study team for further assessment and analysis.

Second, the health communicator will also confirm whether the CMs conduct follow-up according to care plan from the patient’s perspective through regular e-visits.

Third, we will hold regular meetings with the directors of the CHCs, public health officials, and local health officials to ensure the fidelity of the CIC-PDD from the organizational perspective.

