##### Consent to participate in the trial

Within 1 month of the eligibility testing appointment, the study staff will contact PCPs and send the name list of patients who meet the inclusion criteria. Participants will be recruited into the study following contact of the PCPs and will be set up baseline assessments (offline) that will be conducted by blinded outcome assessors. Participants will provide written consent before completing the baseline questionnaire.

In the informed consent document, participants will be explicitly queried regarding their willingness to permit the utilization of their data in the event of their withdrawal from the trial. Additionally, participants will be asked to grant permission to the research team for sharing pertinent data with individuals from Peking University engaged in the research or relevant regulatory authorities, as appropriate. Importantly, this trial does not encompass the collection of biological specimens for storage.

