### Data collection plan

Following the completion of the trial, all collected data will undergo analysis to develop an implementation blueprint. The outcomes, measures, and methods presented in this protocol have been evaluated for relevance and feasibility, and they were designed in collaboration with key stakeholders.

The data for the CIC-PDD project consists of interviewer-based data (face-to-face) and register data. Participants are interviewed face to face at baseline, and again after 6 and 12 months. Data collection through interviews will be conducted by outcome assessors trained in the specific instruments.

See Table 1 for schedule of enrolment, interventions, and assessments.

**Table 1 Tab1:** Schedule of enrolment, interventions and assessments

Assessment level	Construct	Metric/Measure	Data Sources	Data type

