***Effectiveness***				
Individual	Primary outcomes	▪ Primary outcomes: glycemic control (HbA1c); depression symptoms scores (SCL-20)	Health records; survey data	Quantitative
	Mental and physical health outcomes:	▪ Proportion of participants achieving significant reductions in individual outcomes: [50% ≥ reduction in SCL-20], [HbA1c ≥ 0.5% reduction]	Survey data	Quantitative
	Change in quality of life	▪ SF-12 ▪Diabetes Quality of Life	Survey data	Quantitative
	Experience of holistic patient-centered care	▪PACIC ▪Satisfaction with care	Interview data (interviews with patients); survey data	Qualitative & quantitative
	Person-centered care	▪PCCA	Survey data	Quantitative

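### The protocol contradicts itself on how HbA1c, a primary outcome, is obtained, so its ascertainment may differ between arms

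*Protocol article*

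**What the plan says.** All references are to the protocol article.

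- **Primary outcome.** The trial measures change in SCL-20 and in "glycemic control (HbA1c) from baseline to 6 and 12 months".
- **Specimens.** The Health care utilization section says "There will be no biological specimens collected", without qualification. The section Consent to participate in the trial is narrower: "this trial does not encompass the collection of biological specimens for storage".
- **Data types.** The Data collection plan says: "The data for the CIC-PDD project consists of interviewer-based data (face-to-face) and register data".
- **Nature of the primary evaluations.** The Assessments section says: "The primary effectiveness evaluations consist of patient-reported outcome measures".
- **Table 1, Effectiveness.** One row covers both primary outcomes and names health records and survey data as the source, without saying which serves which. The next row holds the responder outcomes, including an HbA1c reduction of at least 0.5%, and names survey data only.
- **Intervention sessions.** The component list under Intervention design says "depression symptoms and HbA1c are measured at all sessions". There are up to 18 sessions in a year, in person or by telephone. The case manager's listed duties and the account of sessions 3–13 refer instead to blood glucose. Supervision and fidelity does too, describing the Follow-up Booklet as recording "PHQ-9 scores, blood glucose level, and what interventions patients accepted".
- **Control arm.** Patients receive enhanced usual care, which includes routine diabetes management. No HbA1c testing is described for them beyond that.
- **Blinding.** Recruited outcome assessors are blinded; the care team, which includes the case managers, is not.

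**The concern.** HbA1c cannot be had by interview, and it cannot be had without blood. A reader of the article cannot tell whether this primary endpoint is measured by the trial, reported by the patient or extracted from routine records.

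The extraction route carries the risk. If case managers test HbA1c as part of the intervention and those results enter the records, the intervention arm has values produced on a protocol schedule by unblinded staff. The control arm has values only when routine care happened to order a test. Number, timing, completeness and blinding of the endpoint could then all depend on arm.

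The protocol recognises a related hazard for its other primary outcome. It uses SCL-20 rather than PHQ-9 because PHQ-9 is used repeatedly in care. No such separation is stated for HbA1c, although the collaborative meetings in the intervention arm also review it.

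**Working it through.** The article gives no figure to reproduce, so the check is to see what each combination of its statements implies. Two statements matter: whether specimens are ruled out altogether or only for storage, and whether sessions measure HbA1c or blood glucose.

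| Specimens | Sessions measure | What follows for the HbA1c outcome |
|---|---|---|
| None at all | HbA1c | The two conflict, unless session tests count as care rather than trial collection. In that case records could hold up to 18 values per intervention patient in the year, against an unstated number of routine values per control patient. Ascertainment may differ by arm. |
| None at all | Blood glucose | Sessions add no HbA1c values. The outcome rests on routine records or self-report in both arms. |
| None stored | HbA1c | The 6- and 12-month assessments can supply HbA1c alike in both arms, but the intervention arm has a second set of values and nothing says it is kept out of the outcome. |
| None stored | Blood glucose | The common assessments can supply HbA1c alike in both arms. Only wording errors remain. |

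The article contains text for all four cells and no statement that chooses between them. Table 1 does not settle it: the joint source leaves records possible for HbA1c, while the responder row, built on the same variable, leaves them out. The patient-reported label fits HbA1c in none of the cells.

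**Size.** In one arm, let *u* be the share without a usable 12-month value and *d* the mean change from baseline in tested patients minus that in untested patients.

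- True mean change = tested mean − *u* × *d*, so the observed mean is off by *u* × *d*.
- With the same *d* in both arms, the control-minus-intervention contrast is off by *d* × (*u* control − *u* intervention).

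Neither *u* nor *d* is given. As an illustration on assumed inputs only:

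- *d* = 0.5 points, 40% untested in control, 5% in intervention: 0.5 × (0.40 − 0.05) = 0.175 points.
- *d* = 0.5 points, 20% and 5% untested: 0.5 × (0.20 − 0.05) = 0.075 points.
- Equal shares untested, or *d* = 0: 0 points.

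With more untested in the control arm, a positive *d* favours the intervention and a negative *d* works against it.

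**The case against.** A reader might infer that ascertainment does differ by arm and that control patients have nothing but routine records. The document does not support that, for four reasons.

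- Face-to-face assessments at baseline, 6 and 12 months apply to both arms, and outcome assessors are blinded. HbA1c could be taken there on equal terms. The responder row that lists survey data alone points the same way.
- The consent section limits the specimen statement to storage. If the flat statement means the same, it no longer bars a test at those visits.
- HbA1c at every session is contradicted in three places and sits badly with telephone sessions. Nothing says that session values feed the outcome.
- Table 2, cited for data sources, is not visible here. Assay, laboratory and window are details that an article commonly leaves to the full protocol.

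It is equally tempting to attach a bias figure. The inputs above are invented, and the protocol anticipates only 10–15% loss to follow-up. The outcome is change from baseline, with analyses adjusted for baseline characteristics, so a stable difference in level between tested and untested patients would largely cancel. Multiple imputation is planned and can help if testing depends on observed data. The 0.5-point figure is a responder threshold for individuals, so it is no yardstick for a between-arm bias.

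All of this stands, and it limits the finding to a risk. It does not remove the contradiction. Missing detail can be left to another document, but statements that exclude one another cannot, and Table 2 could not cancel the unqualified specimen sentence or its conflict with the session text.

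**Conclusion.** The contradiction is established from the text: on specimens, data types, data source, the patient-reported label and what is measured at sessions, the article makes statements about a primary outcome that cannot all be true. Differential ascertainment is a possible consequence. It would arise if HbA1c is taken from records and if session HbA1c values enter those records, and neither condition is confirmed or excluded. The size of any bias cannot be derived from the document. The illustrative 0 to 0.175 points shows only how the result depends on unequal testing and on tested and untested patients differing in change. The point deserves correction because it concerns a primary endpoint and the protection is cheap.

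**What to change.** 1. Reconcile the intervention component list, the consent section, the Data collection plan, Table 1, the Assessments section and the Health care utilization section with the case manager's duties, the account of sessions 3–13, Supervision and fidelity, and the primary outcome definition. Whether sessions measure HbA1c or blood glucose is for the trial team to settle; the text should then say the same throughout.
2. State one HbA1c source, method and time window, identical in both arms and tied to the blinded 6- and 12-month assessments. Split the Table 1 source by outcome, and give the responder outcome the same source as the variable it is built on.
3. If records must be used, apply the same pre-set window to both arms and report completeness by arm.
4. State that case-manager session values are not used for the outcome.

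The cost is protocol wording and one data-source rule. The downside is that some record values outside the window become missing. On timing, recruitment ran from 1 December 2022 to 20 January 2023 and the article is dated 22 August 2023. If follow-up counts from recruitment (an assumption), the 12-month assessments fall around December 2023 to January 2024, so at publication the rule could still precede them. The 6-month assessments would already have taken place, and for those the source actually used should be documented by arm.

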### Process evaluation

We will conduct a nested process evaluation in conjunction with the main analysis of quantitative results from the study. The process evaluation aims to explore the following objectives: (1) whether and how CIC-PDD project are implemented as intended (feasibility and acceptability), (2) to what extent this implementation aligns with the theory CIC-PDD project (consistency), and (3) which outcome has the greatest effectiveness and under what conditions or circumstances (sustainability).

In the process evaluation, the theories mentioned above (CFIR, RE-AIM, BCT, and NPT) are used to provide an overarching framework.

Furthermore, we will utilize a mixed-methods approach, combining qualitative and quantitative data throughout the study process. This approach includes administrative data, checklists, and logs completed at intervention sites, as well as surveys, semi-structured interviews, and focus group discussions.

### Health economics analysis

The objective of the economic analysis is to assess the relative cost-effectiveness of the CIC-PDD project.

The primary outcomes of the economic evaluation will be the incremental cost-effectiveness ratio (ICER) and the probability of cost-effectiveness, derived from the cost-effectiveness acceptability analysis. The measure of patient outcome will be quality-adjusted life years (QALYs) gained at the end of scheduled follow-up. To calculate health expenditures, costs will be classified as direct medical costs for health utilization, direct nonmedical costs (patient self-report), indirect costs (patient self-report), and costs of the intervention (e.g., costs of the training).

In the primary analyses, the perspective of health and social care service providers and patients will be taken into account. The cost-effectiveness acceptability curve (CEAC) will be derived from the analysis of covariance (ANCOVA) to estimate the probability of CIC-PDD project being more cost-effective than usual care across a range of ceiling thresholds.

We will conduct sensitivity analyses to examine the effects of varying discount rates, intervention costs, and effectiveness.

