### Randomization and recruitment

#### Randomization

We randomized CHCs in each county on a 1:1 ratio, with an equal number of CHCs (*n* = 4) in each group. The allocation to the two arms was balanced based on size of the cluster, using the number of diabetic patients in each cluster.

Before implementation, allocation of clusters to each study arm was conducted by a statistician at the Peking University China Center for Health Development Studies. The statistician was not involved in implementation of the study.

To reduce the likelihood of bias caused by contamination and type II errors, cluster randomization was chosen. Patients within the clusters are allocated to the same group as their PCPs.

See Fig. 1 for an illustration of the randomization process.

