#### Sample size and power calculations

The study is powered to detect between-arm differences in achieving the primary outcome at 12 months post-randomization. Based on previous literature [47], a sample size of 480 patients (240 per group) at 8 CHCs offered greater than 80% power (*α* = 0.05; intraclass correlation coefficient 0.03) to detect a 20% absolute risk difference between groups on the primary outcome. To account for a potential 10–15% loss to follow-up (e.g., leave the area, die or refuse to take part in the study at follow-up) and to provide greater robustness against type II error, 280 cases were included in each of the two groups in the actual study. According to our previous systematic review [28], previous study sample sizes ranged from 58 to 417. Therefore, we expect that our study will have the largest sample size and, consequently, the highest efficiency and statistical power.

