### Analysis

All analyses in CIC-PDD study will be performed based on an intention-to-treat statistical principle, adjusted for baseline characteristics [61]. Baseline, 6-month, and 12-month outcomes will be summarized by intervention arm and overall. The results will be presented as means (SD), medians (IQR), or numbers and proportions, as appropriate, with clustering taken into account.

Preliminary analysis will be conducted after the data have been cleaned to determine the pattern of missing baseline and follow-up data. We will conduct exploratory analyses to confirm expected distributions and assess the prevalence and patterns of missing data. Appropriate estimation techniques, such as multiple imputations, will be used to estimate missing data. Additionally, we will compare baseline characteristics between intervention and control group. The distribution of potential confounding factors will be taken into account as well as the participants who were able to complete baseline assessments and those who were unable to do so.

A multivariate regression model will be employed to estimate the effect of CIC-PDD on outcomes, accounting for potential confounding variables, including a random effect for CHCs and cluster size. Furthermore, we will explore the causal mechanism to gain a deeper understanding of how and why the results occur. Heterogeneity in treatment effects across sites and some baseline characteristics (e.g., sex, age, socioeconomic status) will be tested with interaction terms between these variables and the treatment status. To mitigate this effect of within-cluster correlation on estimator accuracy, we will cluster standard errors by CHCs. Moreover, sensitivity analysis will be carried out to check the robustness.

Additionally, we will conduct qualitative analysis to gain a better understanding of the implementation and policy processes, as well as to provide further insight into the results. All interviews and group discussions will be recorded and transcribed to capture the full information. Thematic analysis will be carried out on all qualitative data to identify themes. The theories outlined above will serve as the basis for developing interview topic guides and a coding framework.

Interim analyses and formal stopping rules are implemented to ensure the safety of participants and maintain integrity of the study results.

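### The cost-effectiveness acceptability curve rests on ANCOVA with no stated allowance for the eight randomized CHCs; if run as named, its probabilities would be overconfident

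*Protocol article*

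**What the plan says.** In the Health economics analysis section of the protocol article, "The primary outcomes of the economic evaluation will be the incremental cost-effectiveness ratio (ICER) and the probability of cost-effectiveness". The effect side is also fixed there: "The measure of patient outcome will be quality-adjusted life years (QALYs) gained at the end of scheduled follow-up". For the curve itself the section names one technique: "The cost-effectiveness acceptability curve (CEAC) will be derived from the analysis of covariance (ANCOVA", applied over a range of ceiling thresholds. The section does not mention CHCs, clustering or the Analysis section.

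The Analysis section comes next. Its opening sentence covers everything: "All analyses in CIC-PDD study will be performed based on an intention-to-treat statistical principle, adjusted for baseline characteristics". Further down, the model for the effect of the intervention on outcomes is described as "accounting for potential confounding variables, including a random effect for CHCs and cluster size", and the same paragraph adds "we will cluster standard errors by CHCs".

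Under Randomization, CHCs were allocated 1:1 "with an equal number of CHCs (*n* = 4) in each group". Under Sample size and power calculations, the plan allows for within-cluster correlation through an "intraclass correlation coefficient 0.03".

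**The concern.** The article states a clustered model for outcomes and, separately, a conventionally unclustered one for a primary economic output. An analyst who follows the economics section literally would fit a patient-level ANCOVA with independent residuals, although the unit of randomization was the CHC and there are only four per arm.

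The height of the curve at each threshold depends directly on the standard error of incremental net benefit. If that standard error is too small, every probability is pushed away from 0.5: values above it look too favourable and values below it too unfavourable. The Discussion says the results are meant to feed into policy and practice guidelines, so the certainty attached to this probability matters.

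**Working it through.** **Is there a figure to reproduce?** Not in the economics section: it plans a probability of cost-effectiveness but states none. The check therefore asks how far a single-level analysis would be off under the plan's own clustering assumption.

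**Inputs**
- 480 patients in 8 CHCs (Sample size and power calculations): m = 480/8 = 60 per CHC.
- 280 included per arm in 4 CHCs (same section and Randomization): m = 280/4 = 70 per CHC.
- Intraclass correlation (ICC) 0.03, given for the primary outcome. None is given for costs, QALYs or net benefit, so 0.03 is borrowed and varied from 0.01 to 0.05.
- Equal cluster sizes are assumed.

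**Formulas**
- Design effect: DE = 1 + (m − 1) × ICC.
- Factor by which a single-level standard error is too small: √DE.
- A naive probability P becomes Φ(z(P)/√DE). With a t distribution on 8 − 2 = 6 degrees of freedom, Φ is replaced by that distribution function.

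**Main case (m = 60, ICC 0.03)**
- DE = 1 + 59 × 0.03 = 2.77, and √2.77 = 1.664.
- Naive 0.95: z = 1.645; 1.645/1.664 = 0.988; Φ(0.988) = 0.838. On t with 6 df it is 0.819.
- A nominal 95% interval for incremental net benefit would cover 2 × Φ(1.96/1.664) − 1 = 0.761.

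**Range**

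| ICC | m | DE | SE factor | naive 0.90 becomes | naive 0.95 becomes | naive 0.95, t with 6 df |
|---|---|---|---|---|---|---|
| 0.01 | 60 | 1.59 | 1.26 | 0.845 | 0.904 | 0.880 |
| 0.03 | 60 | 2.77 | 1.66 | 0.779 | 0.838 | 0.819 |
| 0.03 | 70 | 3.07 | 1.75 | 0.768 | 0.826 | 0.808 |
| 0.05 | 60 | 3.95 | 1.99 | 0.740 | 0.796 | 0.780 |

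**Does the Analysis section already cover the curve?** Taking its three provisions in turn:
- The sentence about all analyses extends intention-to-treat and baseline adjustment. It does not mention clustering.
- The CHC random effect belongs to the regression for the effect on outcomes.
- The clustered-error sentence sits in that same paragraph. It names no economic quantity, but excludes none.

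The extension to the curve is therefore possible but not stated.

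**The case against.** The strongest reply is that the article nowhere says clustering is set aside. ANCOVA means a covariate-adjusted comparison of arms, which fits the baseline adjustment required of all analyses, and it can carry a CHC random effect or clustered standard errors. QALYs are described as a patient outcome, so the provisions for outcomes could be read to include them. The article is also condensed: it says the complete protocol is available on request, and a full economic plan may settle the matter.

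Much of this stands. A reader might infer that the economic analysis ignores the CHCs; the text does not support that as a fact, and the finding has to be conditional. What remains is that the section does not leave the method open. It names one that is single-level in ordinary usage, for a primary economic output, with no link to the clustered model.

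A reader might also infer that ANCOVA loses the correlation between costs and QALYs and that this too makes the curve overconfident. That does not follow. An ANCOVA on patient-level net benefit at each threshold includes the covariance automatically. It would be lost only if separate cost and QALY models were combined as independent, which the article does not say. Nor is the direction fixed: Var(NB) = λ²Var(E) + Var(C) − 2λCov(E,C). With λSD(E) = SD(C) assumed, an independence-based 0.90 becomes 0.85 at a correlation of −0.5 but 0.97 at +0.5.

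**Conclusion.** The point holds in conditional form. The economics section derives the acceptability curve from a conventionally single-level method and does not carry over the CHC random effect and clustered standard errors given for outcomes. If ANCOVA is run as named, the probability of cost-effectiveness will be overstated wherever it exceeds 0.5: about 0.84 instead of a naive 0.95, with 0.90 to 0.80 over ICCs of 0.01 to 0.05.

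This rests on three assumptions: that no cluster term is added to the ANCOVA, that net benefit has an ICC in that range (the documents give none), and that there are about 60 equally sized CHC samples' worth of patients per center. At 70 per CHC the error is slightly larger. Because no probability has been stated, this concerns a planned output and not a wrong reported figure. It does not touch the clinical effectiveness analysis.

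**What to change.** In the Health economics analysis section, replace the bare reference to ANCOVA with a statement that the acceptability curve and the uncertainty around the ICER will come from a net-benefit regression at each ceiling threshold, or an equivalent joint model of costs and QALYs. The model should be adjusted for the same baseline covariates as the outcome model, include a CHC random effect, and use small-sample inference suited to eight CHCs (for example a t reference with 6 degrees of freedom). If the full protocol or economic plan already specifies this, a cross-reference is enough.

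The cost is a sentence of text and slightly more programming; recruitment, data collection and trial conduct do not change. The downside is a flatter curve that will favour the intervention less clearly if the naive probability is above 0.5.
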